#### **14.3 Independent Ethics Committee/Institutional Review Board**

The study protocol and any relevant materials provided to the subjects (such as subject information or study description) as well as any advertisements and compensations provided to the subjects will be submitted to the Independent Ethics Committee (IEC) by the investigator. Ethical approval must be obtained before the start of the study and documented in the form of a letter from the investigator, including the

date the Ethics Committee met and granted consent.

After receiving the approval letter from the Independent Ethics Committee, the investigator should also submit the protocol to the Ethics Committee according to the procedures and regulatory requirements.

## **15. Publication and patent of trial results**

The trial results are owned by Chia Tai Tianqing Pharmaceutical Group Nanjing Shunxin Pharmaceutical Co., Ltd. The investigator (study site) should obtain the consent of Chia Tai Tianqing Pharmaceutical Group Nanjing Shunxin Pharmaceutical Co., Ltd. before publishing the paper. Before the main study results are officially published, the investigator (study institution) should exchange the clinical trial results at the academic conference with the prior consent of Chia Tai Tianqing Pharmaceutical Group Nanjing Shunxin Pharmaceutical Co., Ltd.

The patent application for the technical solution (including but not limited to the selection of indications and dose) agreed in this project shall be exclusively owned by CHIA TAI TIANQING Pharmaceutical Group CO., LTD. In the process of clinical trials, clinical research institutions shall jointly apply for patents with CHIA TAI TIANQING Pharmaceutical Group CO., LTD for innovative achievements independently completed by the agreed clinical protocol. CHIA TAI TIANQING Pharmaceutical Group CO., LTD and its Affiliates may manufacture, use, sell, sell, commercialize the products covered by the above patents or those obtained by patent methods. However, without the permission of either party, neither party may transfer or in any way permit a third party to exploit such patent.

## **16. Estimated Trial Schedule**

Proposed start time: November 2021 (after approval by the Ethics Committee) .

Estimated duration of trial: November 2021-November 2023.

**Attachments One calculation formula**

## 1. Cockcroft-Gault creatinine clearance calculation formula

$$\text{Ccr} = [(140 - \text{age}) \times \text{body weight (kg)}] / [72 \times \text{Scr (mg/dL)}], \text{ unit: mL/min}$$

Note: (calculated result  $\times$  0.85 for female subjects)

## 2. QTc calculation Bazetts correction formula

$$\text{QTc} = \text{QT} / (\text{RR}^{0.5}); \text{RR is normalized heart rate value, RR} = 60 / \text{heart rate}$$

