#### **2) Repeat-Dose Toxicity Studies**

##### **4-week toxicity test of intravenous injection in cynomolgus monkeys**

A total of 40 cynomolgus monkeys were used in this study and divided into 4 groups, 10 monkeys in each group (F: M = 1:1): control group (TQB2858 injection (blank)) and TQB2858 20, 60 and 200 mg/kg groups. Once weekly for 4 consecutive weeks (5 doses in total). For dosing groups, toxicokinetic blood samples were collected before the first (Day 1) dosing and at 0, 3, 8, 24, 48, 72, 120 and 168 hours after the end of dosing, before the 3rd and 4th (Days 15 and 22) dosing and at 0 hours after the end of dosing, and before the 5th (Day 29) dosing and at 0, 3, 8, 24, 48, 72, 120, 168, 216, 264, 336, 504, 672 and 1008 hours after the end of dosing. Immunogenicity was measured at 0 h before administration, 336 h and 672 h after administration, and on days 7, 14, and 28 of the recovery period in the treatment group. The plasma concentration and time change of this product in cynomolgus monkey serum were

determined by ELISA, and the immunogenicity of anti-this product antibody in serum was determined by ELISA. All methods were methodologically validated.

Decreased peripheral blood RBC, HGB and HCT and increased RET and RET% were observed in the 60 and 200 mg/kg groups, and mild increase in the proportion of red blood cells and late erythroblasts in the bone marrow smear was also observed in the 200 mg/kg group. The above changes were related to the pharmacological action of this product. By the end of recovery period, the above indicators of monkeys in each dose group showed recovery to varying degrees. At the end of treatment, minimal mononuclear cell infiltration in thyroid gland was observed in  $\geq 20$  mg/kg group, minimal ~ mild mononuclear cell infiltration in kidney was observed in  $\geq 60$  mg/kg group, and minimal mononuclear cell infiltration in meninges was observed in 20 mg/kg and 200 mg/kg groups, which were adverse reactions related to pharmacological effects. Similar reports were also found in the study data of marketed PD-L1 monoclonal antibody. At the end of recovery period, except that meningeal lesions in 200 mg/kg group showed no significant recovery, other organ lesions showed recovery to some extent. After intravenous infusion in cynomolgus monkeys, anti-drug antibodies were detected after drug administration in 9 (9/10), 9 (9/10) and 3 (3/10) animals in each dose group, respectively.

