#### 4.2 Exclusion criteria for subjects

Patients with any of the following criteria will not be included in the trial:

- 1) Concomitant diseases and medical history:
- a) History or presence of other malignancy within 2 years. Patients with the following two situations can be enrolled: Other malignant tumors treated by single surgery can achieve R0 resection without recurrence and metastasis; Cured cervical carcinoma in situ, non-melanoma skin cancer, nasopharyngeal carcinoma and superficial bladder tumors [Ta (non-invasive tumor), Tis (carcinoma in situ) and T1 (tumor infiltrating basal lamina)];
- b) Unresolved toxicity greater than CTCAE Grade 1 due to any prior therapy, excluding alopecia, peripheral sensory neuropathy;
- c) Major surgical treatment or significant traumatic injury (excluding needle biopsy, endoscopic biopsy, etc.) within 28 days before the start of study treatment;
- d) Wounds or fractures that have not been healed for a long time;
- e) Hyperactive/venous thrombotic events within 6 months, such as cerebrovascular accident (including temporary ischemic attack, cerebral hemorrhage, cerebral infarction), deep venous thrombosis and pulmonary embolism;

- f) Patients with a history of psychotropic drug abuse and unable to quit or with mental disorders;
- g) Subjects with any severe and/or uncontrolled disease including:
  - 1. Unsatisfactory blood pressure control (systolic blood pressure  $\geq 150$  mmHg or diastolic blood pressure  $\geq 100$  mmHg);
  - 2. Patients with unstable angina pectoris/cardiac chest pain  $\geq$  grade 2; myocardial infarction  $\leq 12$  months before enrollment; heart failure  $\geq$  grade 1 (New York Heart Association (NYHA) classification); restrictive cardiomyopathy; atrioventricular block  $\geq$  grade 2, arrhythmia not stably controlled by drugs [including QTc  $\geq 450$  ms (male), QTc  $\geq 470$  ms (female)] and arrhythmia that may have potential impact on the trial treatment;
  - 3. Active infection ( $\geq$  CTCAE grade 2 infection);
  - 4. Decompensated cirrhosis, active hepatitis \*;  
\* Active hepatitis (hepatitis B reference: HBsAg positive, and HBV DNA  $> 2500$  copies/mL or  $> 500$  IU/mL; hepatitis C reference: HCV antibody positive, and HCV virus test value exceeds the upper limit of normal); note: eligible subjects with hepatitis B surface antigen positive or core antibody positive, hepatitis C patients, continuous antiviral therapy is recommended to prevent viral activation.

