### 4) 12-Electrocardiogram

For ECG continuous variables, number, mean, standard deviation, median, quartiles, minimum and maximum will be described at baseline and each visit by dose group, and mean, standard deviation and 95% CI will be described for changes from baseline.

The ECG examination results at each visit will be descriptively summarized for each dose group, and classified into normal, abnormal without clinical significance and abnormal with clinical significance. Cross-classification table will be used to compare with baseline ECG results.

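### Bazett is the protocol's only QTc correction; reporting the cube-root correction and heart-rate change beside it would guard the single-arm ECG summaries against misreading a heart-rate shift

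*Protocol*

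**What the plan says.** Attachment One of the protocol (calculation formulas), item 2, is headed "QTc calculation Bazetts correction formula". It sets QTc = QT/RR^0.5 with RR = 60/heart rate. No other QTc correction appears in the protocol.

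Section 11.3.5 4) (12-lead ECG) states: "For ECG continuous variables, number, mean, standard deviation, median, quartiles, minimum and maximum will be described at baseline and each visit by dose group", and then "mean, standard deviation and 95% CI will be described for changes from baseline". It does not list the variables, so QTc is not named. ECG findings are also classed by clinical significance and cross-tabulated against baseline.

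The visit schedule places an ECG at screening, on C1D7, C1D14 and C1D21, on day 21 of each later cycle, and at the exit visit. Pulse is one of the vital signs. Section 11.3.5 5) summarises vital signs by visit, also with mean, SD and 95% CI of the change from baseline.

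QTc also appears in section 4.2, where limits of 450 ms (male) and 470 ms (female) stand under "arrhythmia not stably controlled by drugs". Section 11.3.2 plans no hypothesis test, and the protocol has no on-treatment QTc threshold.

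**The concern.** A QT correction removes heart rate only if its exponent matches the way QT varies with RR in the patients studied. If QT varies as RR^b, Bazett's QTc keeps a factor RR^(b − 0.5). For b below 0.5 it rises when the heart speeds up and falls when it slows, with no change in repolarisation.

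In a randomised trial, a heart-rate shift common to both arms would largely cancel. This trial has one arm, so a mean change from baseline in QTc stands alone with its confidence interval. A faster pulse could look like QT prolongation, and a slower one could mask it. Some shift in pulse is conceivable: the 4-week monkey study reports "Decreased peripheral blood RBC, HGB and HCT" at its two higher doses. At stake is the reading of a descriptive safety table. Safety is the secondary objective.

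**Working it through.** **Inputs from the protocol**
- Correction: QTcB = QT/RR^0.5, RR = 60/HR (Attachment One, item 2).
- Summary: mean change from baseline with 95% CI for continuous ECG variables (11.3.5 4)), single arm.

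**Assumptions (the documents give none of these)**
- True QTc, meaning QT at 60 bpm, is 410 ms and does not change on treatment.
- QT = 410 × RR^b, with b = 0.25, 1/3, 0.40 or 0.50.
- Heart rate moves from 75 bpm (RR = 60/75 = 0.800) to 85 bpm (RR = 60/85 = 0.706).

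**Check of the formula.** At 60 bpm RR = 1, so a QT of 400 ms gives QTcB = 400 ms. The formula is written correctly. The protocol states no ECG result to reproduce.

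**Artefact under each correction**

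For a correction with exponent c, QTc = QT/RR^c = 410 × RR^(b − c). The false change is 410 × (0.706^(b − c) − 0.800^(b − c)).

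For Bazett (c = 0.5) and b = 1/3: 0.706^(−1/6) = 1.0598 and 0.800^(−1/6) = 1.0379. The difference is 0.0219, and 410 × 0.0219 = +9.0 ms.

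For the cube root (c = 1/3) and b = 0.50: 0.706^(1/6) = 0.9436 and 0.800^(1/6) = 0.9635. The difference is −0.0199, and 410 × (−0.0199) = −8.2 ms.

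| True b | False change, QTcB | False change, QTcF |
|---|---|---|
| 0.25 | +13.8 ms | +4.4 ms |
| 1/3 | +9.0 ms | 0 ms |
| 0.40 | +5.3 ms | −3.4 ms |
| 0.50 | 0 ms | −8.2 ms |

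Neither correction is free of heart rate across the whole range. Where both show the same change, the reading is robust. Where they disagree and heart rate has moved, the disagreement is the warning.

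**The case against.** The case against is substantial, and most of it stands.

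- **QTc is not named in 11.3.5 4).** Both formulas in Attachment One, creatinine clearance and QTc, serve eligibility criteria, so their use in the safety tables is inferred. The list of tabulated ECG variables is also something a statistical analysis plan may settle. The inference is reasonable, because QTc is a continuous ECG variable with one defined formula, but it remains an inference.
- **A heart-rate shift would not go unseen.** Pulse change is already summarised in 11.3.5 5). It is not set beside the QTc change, however, and no table is said to relate the two.
- **The animal data do not show a pulse shift.** Section 1.3.1.2 reports no damaging effect on the cardiovascular system, and the 4-week study reports no significant ECG or blood pressure abnormality. The red-cell changes occurred at 60 and 200 mg/kg with varying recovery, and the thyroid infiltration was minimal.
- **No decision hangs on it.** There is no hypothesis test and no QTc-based treatment rule.

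Three stronger readings are tempting, and the documents support none of them.

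First, a reader might infer that the trial will probably report a false QTc signal. With an assumed mean rise of 10 bpm (SD 10), an SD of 15 ms for the true QTc change and b = 1/3, simulation puts the share of trials whose 95% CI for QTcB excludes zero at about 70% with 30 patients. That share falls to 23% for a 5 bpm rise, 10% for 3 bpm and 5% for none. With 10 patients and a 10 bpm rise it is about 27%. These rates are set by the assumptions.

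Second, a reader might infer that the cube-root correction is right and should replace Bazett. At b = 0.50 the error passes to QTcF, whose interval then excludes zero in about 70% of trials with 30 patients and the same 10 bpm rise.

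Third, a reader might infer that the entry limit is defective because 450 ms by Bazett equals 464 ms by the cube root at 50 bpm and 413 ms at 100 bpm. That is a difference between two formulas, and it is Bazett's error only if the cube root is taken as true. Attachment One already names the formula, and the limit is a clinical rule.

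**Conclusion.** The point holds as a cheap improvement to descriptive safety reporting. Nothing in the protocol is contradicted or miscalculated. With Bazett as the only stated correction and no control arm, a mean heart-rate shift could be misread as a QTc change if QTc is among the summarised ECG variables and b differs from 0.5. For a 75 to 85 bpm shift at 410 ms, the size is between 0 ms (b = 0.50) and about 14 ms (b = 0.25). The exponent, the shift and the 410 ms are all assumptions, and with no heart-rate shift there is no artefact at any b. ORR is unaffected.

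**What to change.** 1. In Attachment One, add QTcF = QT/RR^(1/3) for use in the safety tables. Keep Bazett's formula as written.
2. In section 11.3.5 4), name QTc among the continuous ECG variables. Report change from baseline in QTcF, QTcB and ECG heart rate side by side at each visit.
3. Report the slope of each QTc on heart rate in the baseline ECGs, so that the data show which correction fits better. Do not presume that it is QTcF. The schedule gives one screening ECG per patient, so the slope describes differences between patients and may be imprecise; it is a guide to reading the tables.
4. Leave the 450/470 ms entry criterion unchanged.

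The cost is one formula line and one extra derived variable in descriptive tables. It uses QT and heart rate, which the Bazett formula already needs, so no further ECGs or patients are required.

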**APPENDIX II: EVALUATION OF QUALITY OF LIFE (ECOG PS) (5 POINTS)**

---

|   |                                                                                                                                                                   |
|---|-------------------------------------------------------------------------------------------------------------------------------------------------------------------|
| 0 | Normal activity                                                                                                                                                   |
| 1 | Mild symptoms, self-care, able to engage in light physical activity                                                                                               |
| 2 | Can tolerate the symptoms of the tumor and take care of himself/herself, but can stay in bed for no more than 50% of the time during the day                      |
| 3 | The tumor symptoms are severe, with more than 50% of the time in bed during the day, but they can also get up and stand, and some of them take care of themselves |
| 4 | Critically ill Bedridden                                                                                                                                          |
| 5 | Death                                                                                                                                                             |

---

## APPENDIX III NEW YORK HEART ASSOCIATION (NYHA) FUNCTIONAL CLASSIFICATION

| Grading   | New York Heart Association (NYHA) Class                                                                                                                                                             |
|-----------|-----------------------------------------------------------------------------------------------------------------------------------------------------------------------------------------------------|
| Grade I   | No limitation of physical activity, ordinary activity does not cause undue fatigue, dyspnea or palpitation. That is, the compensatory phase of cardiac function.                                    |
| Grade II  | Slight limitation of physical activity. Asymptomatic at rest, fatigue, palpitation, dyspnea, or angina may be precipitated by ordinary activity. It is also known as grade I or mild heart failure. |
| Grade III | Marked limitation of physical activity, absence of symptoms at rest, less than ordinary activity producing the above symptoms. Also known as grade II or moderate heart failure.                    |
| Grade IV  | Inability to engage in any physical activity, congestive heart failure or angina symptoms at rest, aggravated by any physical activity. It is also known as grade III or severe heart failure.      |

Note: Cardiac function is divided into four classes, and heart failure is divided into three classes (slightly supplemented according to NYHA classification) ).
